## Definitions of Adverse Event (AE) and Serious Adverse Event (SAE)

An **Adverse Event** is any untoward medical occurrence in a patient or clinical investigation patient administered a pharmaceutical product and which does not necessarily have to have a causal relationship with this treatment.

A priori, efficacy endpoints as specified in the protocol will not be considered as AEs except if, because of the course or severity or any other features of such events, the Investigator, according to his/her best medical judgment, considers these events as exceptional in this medical condition.

A **Serious Adverse Event** is any untoward medical occurrence that at any dose:

1. • Results in death or;
2. • Is life-threatening or;

Note: The term "life-threatening" in the definition of "serious" refers to an event in which the patient was at risk of death at the time of the event; it does not refer to an event which hypothetically might have caused death if it were more severe.

1. • Requires inpatient hospitalization or prolongation of existing hospitalization or;
2. • Results in persistent or significant disability/incapacity or;
3. • Is a congenital anomaly/birth defect;
4. • Is a medically important event:

Medical and scientific judgment should be exercised in deciding whether expedited reporting is appropriate in other situations, such as important medical events that may not be immediately life-threatening or result in death or hospitalization but may jeopardize the patient or may require intervention to prevent one of the other outcomes listed in the definition above.

Note: Examples of such events are intensive treatment in an emergency room or at home for allergic bronchospasm, blood dyscrasias, convulsions or a asymptomatic increase of ALT (≥10 ULN) that does not result in hospitalization, or development of drug dependency or drug abuse.

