## Identification of adverse events

At each follow-up visit (days 1, 2, 3, 7, 14, 21, 28, and 42, and any unscheduled day), study clinicians will assess patients according to a standardized clinical record form. A severity grading scale, based on toxicity grading scales developed by the WHO and the National Institutes of Health, Division of Microbiology and Infectious Diseases, will be used to grade severity of all symptoms, physical exam findings, and laboratory results as mild, moderate, severe or life threatening (Appendices 2 and 3). Any new event, or an event present at baseline that is increasing in severity, will be considered an adverse event.

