***Serious Adverse Events***

In the case of a Serious Adverse Event the Investigator must immediately:

1. • SEND (within 1 working day, preferably by fax) the signed and dated corresponding page(s) in the Case Report Form **and** the “SAE complementary information” form to

- [name] (address on the cover page)
- [contact] or [contact]
- or [name]: [contact] or [contact]
- ***[contact]***;
- immediately (on the same day) TELEPHONE [name] or the study monitor in the event of death or a life-threatening event;

1. • ATTACH the photocopy of all examinations carried out and the dates on which these examinations were performed. Care should be taken to ensure that the patient's identity is protected and the patient's identifiers in the Clinical Trial are properly mentioned on any copy of source document provided to the Sponsor. For laboratory results, include the laboratory normal ranges;
2. • Follow-up of any Serious Adverse Event that is fatal or life threatening should be provided within one additional calendar week.

- Serious adverse events shall be reported to FOMREC within 7 days while minor adverse events shall be submitted in the annual report.
- Serious adverse events shall be reported to the UNCST and the NDA in prescribed progress reports (annual progress reports).

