APPENDIX 6: Methods of blood sample analyzes

APPENDIX 7: Operational definitions

APPENDIX 8: World Medical Association Declaration of Helsinki

APPENDIX 9: Flow of patients in OPD and Study Clinic

APPENDIX 1Document related to the assessment of judgment criteria

WHO guidelines for assessing response to treatment (2003)

| ETF (Early Treatment Failure):   - Development of danger signs or severe malaria on Days 1or 2 or 3 in the presence of parasitemia - Parasitemia on Day 2 higher than on Day 0, irrespective of axillary temperature - Parasitemia on Day 3 with axillary temperature > 37,5C - Parasitemia on Day 3 > 25% of count on Day 0 |
| --- |
| LCF (Late Clinical Failure):   - Development of danger signs or severe malaria after Day 3 in the presence of parasitemia, without previously meeting any of the criteria of early treatment failure - Axillary temperature > 37,5C ( or history of fever) on any day from Day 4 to 28 in the presence of parasitemia, without previously meeting any of the criteria of early treatment failure |
| LPF ( Late Parasitological Failure):   - Presence of parasitemia on any day from Day 7 to Day 28 and axillary temperature  < 37,5C , without previously meeting any of the criteria of early treatment failure or late clinical failure |
| **ACPR (Adequate Clinical and Parasitological Response)**   - Absence of parasitaemia on Day 28, irrespective of axillary temperature, without previously meeting any of the criteria of early treatment failure or late clinical or parasitological failure |

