**Danger Signs**

- Recent convulsions *(>1 within 24 h)*
- Altered consciousness  *(confusion)*
- Lethargy
  - Unable to drink or breast feed
  - Vomiting everything
  - Unable to stand/sit due to weakness

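### Section 11.3 leaves open whether a serious, non-fatal treatment failure is reported as an SAE, and section 11.2 wrongly limits symptom AEs to drug-related ones

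*Protocol*

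**What the plan says.** Section 11.3 defines an AE without requiring a causal link to treatment. It then removes efficacy endpoints by default: "efficacy endpoints as specified in the protocol will not be considered as AEs except if, because of the course or severity" or other features, the investigator "considers these events as exceptional in this medical condition". No criterion for exceptional is given.

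The SAE definition follows in the same section. An SAE "is any untoward medical occurrence that at any dose" meets one of the listed seriousness criteria, which include threat to life, inpatient hospitalization and medical importance. The examples of medically important events include "blood dyscrasias, convulsions or a asymptomatic increase of ALT".

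Appendix 1 defines the efficacy outcome classes. ETF includes danger signs or severe malaria with parasitaemia on Days 1 to 3. LCF includes "Development of danger signs or severe malaria after Day 3 in the presence of parasitemia". Appendix 4 lists "Recent convulsions" (more than one within 24 hours) among the danger signs.

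Section 11.4 ends: "Any new event, or an event present at baseline that is increasing in severity, will be considered an adverse event". It makes no exception for efficacy endpoints.

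Section 11.2 says that symptoms described at visits are recorded as AEs if they appear or worsen and are attributed to the study drug. Section 11.7 requires all AEs to be recorded whatever their seriousness or relationship. Section 14.5.4.1 plans tables of all TEAEs as well as possibly related ones.

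**The concern.** Two rules in section 11.3 reach the same event with different results, and the protocol does not say how they combine. A failure with danger signs or severe malaria is excluded from AEs as an efficacy endpoint, yet it can satisfy the SAE definition a few lines later.

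The SAE label has practical consequences. Under section 11.7 the sponsor must be told within 1 working day, and "Serious adverse events shall be reported to FOMREC within 7 days". Under section 7.3, SAE notifications go to the safety committee, which may suspend inclusions. Section 14.5.4.1 builds its SAE tables from the same label. A failure recorded only as ETF or LCF does not enter these channels as an SAE. The patients are children enrolled at 6 to 59 months and treated repeatedly over two years, and comparing tolerability is a stated secondary objective.

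The wording of section 11.2 is a separate defect. If it is followed, a symptom judged unrelated to the drug is never recorded as an AE, so for symptoms the table of all TEAEs would show little beyond the possibly related ones.

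**Working it through.** No arithmetic applies: the conflict is between rules, and the protocol gives no severe-malaria rate from which to estimate a number of affected events. The check applies the rules to one case.

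**Case.** On Day 10 after treatment, a child has parasitaemia and two convulsions within 24 hours, and is admitted. The child survives.

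1. *Efficacy class.* Two convulsions within 24 hours exceed the Appendix 4 threshold for a danger sign. With parasitaemia after Day 3, and no earlier ETF, this is LCF under Appendix 1 and hence an efficacy endpoint.
2. *AE exclusion, section 11.3.* As an efficacy endpoint, the event is by default not an AE. It becomes one only if the investigator finds it exceptional for malaria. Appendix 1 itself lists this form of failure, and section 7.2 provides quinine for complicated malaria, so an investigator could reasonably find it not exceptional. Another could rely on the reference to severity and report it. Both follow the text.
3. *SAE definition, section 11.3.* The event is an untoward occurrence that required inpatient hospitalization, and convulsions are a named example of a medically important event. On the wording, it is an SAE. The definition starts from an untoward occurrence, not from an event already accepted as an AE.
4. *Identification rule, section 11.4.* The event is new, so it is an AE.
5. *Symptom rule, section 11.2.* Convulsion is one of the symptoms assessed at every visit under section 10.1.3. If it is attributed to malaria and not to the drug, section 11.2 does not make it an AE.

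Read separately, steps 2 and 5 keep the event out of AE reporting, while steps 3 and 4 bring it in.

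**Does the wording settle the order?** Section 11.2 exempts the social hospitalization during first-attack treatment and names both AE and SAE in doing so. The exclusion in section 11.3 names AEs only. That favours keeping serious failures reportable. On the other side, section 12.1.1 lists danger signs and adverse events as separate reasons for stopping treatment, which suggests that failures were meant to stay out of AE reporting. Neither is an explicit rule.

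**Relatedness.** The AE definition in section 11.3 needs no causal link, and section 11.7 records AEs regardless of relationship. Section 11.2 requires a causal judgement before a symptom counts. These cannot all be followed.

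**The case against.** The best defence is that the exclusion is the specific rule, that an SAE is a kind of AE, and that severity is an express ground for override. Section 11.1 also says that AE assessment at each episode follows the definitions of AE and SAE. Section 11.3 can therefore be read as governing section 11.4, which describes identification at visits. That stands in part: it weakens the conflict with section 11.4. It does not settle the exclusion against the SAE definition, since both sit in section 11.3. The override permits reporting of a serious failure but does not require it.

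Oversight also does not depend wholly on the SAE label. Section 15.4 asks that the ethics and regulatory bodies be informed of any event likely to affect patient safety, and that serious adverse reactions or unanticipated effects be reported immediately. The safety committee may review case report forms with questionable data, and deaths have their own safety variable and table. These safeguards are real and limit the consequence. They do not place a non-fatal serious failure in the SAE tables or fix when it is reported.

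A reader might infer that serious failures go unrecorded, that one arm is favoured, or that the primary result is affected. The protocol supports none of these. The failure is still classified as ETF or LCF and counts in the primary endpoint when it occurs in the first attack by Day 28. The same rule applies to both arms, and section 9.2.2 blinds those who evaluate patients and classify outcomes. Nor does section 11.3 forbid reporting such a failure as an SAE; it leaves the matter to judgement.

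**Conclusion.** The point holds as a defect in the safety-reporting rules. Whether a non-fatal treatment failure that meets a seriousness criterion is reported as an SAE depends on how the investigator reads section 11.3, because the override test is exceptionality and not seriousness. Independently, the relatedness condition in section 11.2 contradicts sections 11.3 and 11.7 and undermines the tables of all TEAEs.

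The conclusion rests on the wording alone and assumes that sites apply these sections as written. Its size cannot be expressed as a number of missed SAEs without a severe-malaria rate. The non-inferiority analysis is unaffected and no between-arm bias is claimed. The severity is minor to moderate: the point should be corrected because correction is cheap and the rules govern safety reporting in young children, but it does not threaten the trial's main conclusion.

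**What to change.** Make three wording changes.

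(a) In section 11.3, state that the efficacy-endpoint exclusion applies only to treatment failures meeting no seriousness criterion. Any ETF or LCF that meets one, other than through the social hospitalization described in section 11.2, is recorded and reported as an SAE regardless of judged relationship to treatment.

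(b) In the last sentence of section 11.4, add an exception for efficacy endpoints excluded under section 11.3, so that the two sections agree for non-serious failures.

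(c) In section 11.2, delete the condition that a symptom must be considered related to the study drug. Relationship is already recorded as a separate item under sections 11.5 and 11.6, so the possibly related tables can still be produced.

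The cost is a protocol amendment of a few lines and a few more AE and SAE forms. No added visits, samples or assessments are needed, since clinical signs are already examined at every visit.

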## Identification of adverse events

At each follow-up visit (days 1, 2, 3, 7, 14, 21, 28, and 42, and any unscheduled day), study clinicians will assess patients according to a standardized clinical record form. A severity grading scale, based on toxicity grading scales developed by the WHO and the National Institutes of Health, Division of Microbiology and Infectious Diseases, will be used to grade severity of all symptoms, physical exam findings, and laboratory results as mild, moderate, severe or life threatening (Appendices 2 and 3). Any new event, or an event present at baseline that is increasing in severity, will be considered an adverse event.

## Severity, relationship of event to study drug and outcome

The severity of a clinical adverse event is to be scored according to the following scale:

1. Mild Awareness of sign or symptom, but easily tolerated

2. Moderate Discomfort enough to cause interference with usual activity

3. Severe Incapacitating with inability to work or perform usual activity

4. Life-threatening Patients at risk of death at the time of the event

If the same event worsens in intensity, a new Adverse Event Form should be completed with the date of worsening, a new intensity, etc

The relationship (Yes or No) to the listed Investigational Product will be reported according to the Investigator's judgment

The outcome of the AE will be assessed at the time of the last patient observation according to the following classification:

| Recovered :  Recovered with sequelae | The patient has fully recovered with no observable residual effects  The AE has resulted in a permanent impairment |
| --- | --- |
| Recovering : | Improvement in the patient’s condition has occurred, but the patient still has some residual effects |
| Not recovered : | The AE has not resolved and remains the same as at onset |
| - Death : | The patient died due to the AE |
| - Unknown : | The outcome of the AE is not known because the patient did not return for follow-up (lost to follow-up) |

## Reporting of adverse events

For each possible adverse event identified and graded as mild, moderate, severe or life threatening, an adverse event report form will be completed. The following information will be recorded for all adverse experiences that are reported:

1. Description of event
2. Date of event onset
3. Maximum severity of the event
4. Maximum suspected relationship of the event to study medication
5. Is the event serious?
6. Outcome
7. Date event resolved

## Obligation of the Investigator regarding safety reporting

***Adverse Events***

All Adverse Events regardless of seriousness or relationship to Investigational Product, spanning from the first visit planned in the Clinical Trial Protocol/signature of the informed consent form, up to the last visit planned in the protocol (D42), are to be recorded on the corresponding page(s) included in the Case Report Form.

Whenever possible, symptoms should be grouped as a single syndrome or diagnosis. The Investigator should specify the date of onset, intensity, action taken with respect to Investigational Product, corrective treatment/therapy given, additional investigations performed, outcome and his/her opinion as to whether there is a reasonable possibility that the Adverse Event was caused by the Investigational Product.

Laboratory, vital signs abnormalities are to be recorded as Adverse Events only if they are medically relevant: symptomatic, requiring corrective treatment, leading to discontinuation and/or fulfilling a seriousness criterion and/or is defined as an AESI.

***Serious Adverse Events***

In the case of a Serious Adverse Event the Investigator must immediately:

1. • SEND (within 1 working day, preferably by fax) the signed and dated corresponding page(s) in the Case Report Form **and** the “SAE complementary information” form to

- [name] (address on the cover page)
- [contact] or [contact]
- or [name]: [contact] or [contact]
- ***[contact]***;
- immediately (on the same day) TELEPHONE [name] or the study monitor in the event of death or a life-threatening event;

1. • ATTACH the photocopy of all examinations carried out and the dates on which these examinations were performed. Care should be taken to ensure that the patient's identity is protected and the patient's identifiers in the Clinical Trial are properly mentioned on any copy of source document provided to the Sponsor. For laboratory results, include the laboratory normal ranges;
2. • Follow-up of any Serious Adverse Event that is fatal or life threatening should be provided within one additional calendar week.

- Serious adverse events shall be reported to FOMREC within 7 days while minor adverse events shall be submitted in the annual report.
- Serious adverse events shall be reported to the UNCST and the NDA in prescribed progress reports (annual progress reports).

***Follow-up***

- The Investigator should take all appropriate measures to ensure the safety of the patients, notably he/she should follow up the outcome of any Adverse Events (clinical signs, laboratory values or other, etc.) until the return to normal or consolidation of the patient's condition. If the AE is graded:
- mild (grade 1), the patient will be managed according to good medical practice and the active follow up will be stopped at the last study visit.
- more than 1, the patient will be followed until the AE resolves, improves, or stabilizes. All information collected after the last visit will be recorded in the source documents.
- Any new relevant information concerning the initial SAE is to be described on the “SAE follow-up information form” by the investigator and sent to [name],
- In case of any Serious Adverse Event, the patient must be followed up until clinical recovery is complete and laboratory results have returned to normal, or until progression has been stabilized. This may imply that follow-up will continue after the patient has left the Clinical Trial and that additional investigations may be requested by the Monitoring Team;
- In case of any Serious Adverse Event brought to the attention of the Investigator at any time after cessation of Investigational Product and considered by him/her to be caused by the Investigational Product with a reasonable possibility, this should be reported to the Monitoring Team.

## Adverse Event of special interest (AESI)

An adverse event of special interest (serious or non-serious) is one of scientific and medical concern specific to the sponsor’s product or program, for which ongoing monitoring and rapid communication by the investigator to the Sponsor may be appropriate. Such events may require further investigation in order to characterize and understand them.

In case of AESI, the Sponsor will be informed immediately (i.e. within 1 working day), even not fulfilling a seriousness criterion, using the AE form together with the SAE complementary form to be sent to the representative of the monitoring team whose name, address and fax number appear on the clinical trial protocol.

All neutropenia with neutrophil count < 400/mm3 and all values of ALAT exceeding 8x upper laboratory normal (ULN) value or ALAT exceeded 3xULN associated to total bilirubin exceeded 2xULN will be considered as AESI. Refer to the specific guideline in Appendix 5 for the management of these AESI.

## Obligations of the Sponsor

During the course of the study, the Sponsor will report in an expedited manner all SAEs that are both unexpected and at least reasonably related to the IP, to the Authorities, IECs / IRBs as appropriate and to the Investigators.

In addition, the Sponsor may report in an expedited manner all SAEs that are expected and at least reasonably related to the IPs to the Authorities, according to local regulations.

Any other AE not listed as an expected event in the Summary of Product Characteristics and in this protocol will be considered as unexpected.

The Sponsor will report all safety observations made during the conduct of the trial in the CSR.

# Handling of patient TEMPORARY OR DEFINITIVE TREATMENT DISCONTINUATION AND OF PATIENT STUDY DISCONTINUATION

The investigational product should be continued whenever possible. Any IP discontinuation should be fully documented in the CRF. In any case, the patient should remain in the study as long as possible.

## Treatment discontinuation with investigational product(s)

### List of criteria for treatment discontinuation

The objective criteria for discontinuing the study treatment and resorting to a safety treatment are as follows:

- Withdrawal of informed consent: The parents/guardians may withdraw the patient from treatment with Investigational Product if they decide to do so, at any time and irrespective of the reason, or this may be the Investigator’s decision
- onset of one or more danger signs/or signs of complicated malaria, according to the WHO definition (cf. Appendix 4),
- parenteral treatment becomes necessary,
- onset of an adverse event justifying treatment discontinuation
- repeated vomiting/rejection

If the patient’s condition progresses in an unsatisfactory manner, he/she will be directed to the centre’s referring facilities.

### Handling of patients after treatment discontinuation

Patients will be followed up according to the study procedures as specified in this protocol up to the scheduled date of study completion (D42), or up to recovery or stabilization of a followed-up AE, whichever comes last.

If possible, and after the discontinuation of treatment, the patients will be assessed using the procedure normally planned for the last dosing day with the Investigational Product (D3) and the final evaluation. After quinine prescription notified, the case report form will be fully completed till D42 and efficacy of quinine will be biologically and clinically evaluated.

